### Specific biochemistry tests

Specific biochemical tests will be considered (Table 2): serum aldosterone (AS); plasma renin activity (PRA); highly sensitive C-reactive protein (hsCRP); metalloproteinase 9 (MMP-9); tissue inhibitors of metalloproteinase (TIMP-1 and TIMP-2); nitrites and nitrates; interleukin-1, 6, 8, 10, and 18 (IL-1, IL-6, IL-8, IL-10 and IL-18); TNF-α, thromboxane B_2_ (TXB_2_); fibrinogen; intercellular adhesion molecule-1 (ICAM-1); plasminogen activator inhibitor (PAI-1); angiotensin converting enzyme (ACE); and angiotensin II (Ang II).

**Table 2 Tab2:** Specific biochemistry tests

Inflammatory markers and endothelial dysfunction	
• IL-1, IL-6, IL-8, IL-18 • TNF-α • hsCRP and fibrinogen • intercellular adhesion molecule (ICAM-1)	
Anti-inflammatory	
• IL-10	
Coagulation	
• plasminogen activator inhibitor (PAI-1) • fibrinogen	
Renin Angiotensin Aldosterone System	
• Ang II • angiotensin converting enzyme (ACE) • plasma renin activity • serum aldosterone	
Extracellular matrix and tissue inhibitors	
• MMP-9 • TIMPs	

*IL* interleukin, *Ang II* Angiotensin II, *TNF-α* tumor necrosis factor alpha, *hsCRP* highly sensitive C-reactive protein, *MMP* metalloproteinase, *TIMPs* tissue inhibitors of metalloproteinase

To evaluate the hsCRP, MMP-9, TNF-α, AS, PRA, TIMPs-1 and −2, nitrites and nitrates, IL-1, IL-6, IL-8, IL-10, IL-18, thromboxane B2, and fibrinogen levels, plasma samples will be obtained after centrifugation at 3500 rpm and 4 °C for 15 min immediately after collection and then stored at −80 °C for later analysis. The IL-1, IL-6, IL-8, IL-10, IL-18, TNF-α, MMP-2 and −9, ACE, and Ang II will be measured using the ELISA technique (R & D systems, Minneapolis, MN, USA) according to the manufacturer’s instructions and as described in a previous study [75]. The hsCRP is determined by a highly sensitive assay with a BN II nephelometer (Dade Behring, Marburg, Germany). The multiplex method will be used to measure the PAI-1 and ICAM-1 inflammatory mediators [14]. Plasma concentrations of tissue inhibitors (TIMP-1 and −2) will be measured using a commercially available enzyme-linked immunosorbent assay (R & D Systems, Minneapolis, MN, USA) according to the manufacturer’s instructions.

The routine PRA assay available today is based on the determination of plasma angiotensin I generated in vitro by the proteolytic action of renin on its substrate: angiotensinogen under predetermined conditions of time and temperature. Blood samples should be collected and maintained with special care: (1) in iced syringes and tubes, (2) using EDTA as a proteolysis inhibitor (angiotensinase), (3) separating the plasma in a refrigerated centrifuge no more than 30 min after each collection, and (4) separating and storing the plasma at −20 °C or less (ideally at −70 °C) until the time of the assay. As the PRA levels fluctuate in response to posture, diet, and hydration (in parallel with the aldosterone system), reference values exist for the various conditions, but most laboratories require that the patient has fasted and rested lying down for at least 30 min before the collection of baseline samples [76].

A commercial kit (Cayman Chemical Co. Ann Arbor, MI, USA) will be used under controlled conditions to measure the total nitrite and nitrate concentrations in the biological fluids and by-products of the production of NO using the NO synthase enzyme. Nitrites and nitrates are stable end products of the NO reaction with molecular oxygen. The proportions of nitrates and nitrites are variable and cannot be accurately determined. Therefore, the best indicator of NO production is the sum of the nitrites and nitrates. The Cayman Chemical kit used to determine nitrites and nitrates provides an accurate and convenient method for measuring the total concentrations through a simple two-step process. This test is based on the determination of nitrite, not of nitrate, using the Griess reaction. The method is very simple, and a large number of samples can be processed in a short time, making it quite suitable for routine application in research laboratories. Plasma samples, collected in an EDTA anticoagulant, are first diluted four times using distilled water and de-proteinized by adding 1/20 volume of zinc sulfate (300 g/L), giving a concentration of 15 g/L. After centrifugation at 10,000 g for 5 min or 1000 g for 15 min at ambient temperature, 100 μL of Griess reagent (1 g/L sulfanilamide, 25 g/L of phosphoric acid, and 0.1/L naphthylethylenediamine dihydrochloride) is added. After 10 min incubation at room temperature, the sample develops a violet color, the intensity of which is measured in a plate reader using a 540-nm wavelength [77]. Each sample will be tested in duplicate. The determination of the standard curve of nitrite concentration will be carried out using the protocol provided by the manufacturer. Subsequently, a graph is drawn to map the intensity of readings at 540 nm to known concentrations of nitrates or nitrites. The total nitrate concentrations (nitrites + nitrates), or nitrates and nitrites in isolation, are calculated by determining the intersection of the spectrophotometer reading. The concentration of the sample is subsequently calculated by the simple rule of three.

Thromboxane B2 will be evaluated in blood samples collected in test tubes containing EDTA. The plasma is separated by centrifugation and stored at −20 °C until testing. The plasma samples are purified using a reversed-phase column (Sep-Pak C18 - Waters Co., Milford, MA, USA), and the TXB_2_ plasma levels (metabolite of TXA_2_) are determined using a commercial enzyme immunoassay kit (ELISA Cayman Chemical Co. Ann Arbor, MI, USA). This assay uses 500 μL of venous blood plasma and is based on the competition between TXB_2_ and a TXB_2_ tracer (TXB_2_ attached to an acetylcholinesterase molecule) with a limited number of TXB_2_-specific rabbit antiserum binding sites. The concentration of the tracer is held constant, while the free TXB_2_ changes. The TXB_2_ antiserum complex (free tracer) binds to a rabbit monoclonal antibody previously attached to the plate, which is rinsed to remove unwanted reagents, and Ellman’s reagent is added (which contains the substrate for acetylcholinesterase). The product of this enzymatic reaction has a yellow color and absorbs 420-nm wavelength light in a spectrophotometer [78, 79].

### Primary outcome measure

The primary outcome measure will be the change from baseline in the peripheral blood pressure of individuals with resistant hypertension after transcutaneous electrical nervous stimulation.

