**Methods/design:**

This is a randomized, single blind (subject), parallel-assignment study controlled with a sham group and including participants aged 40 to 70 years with resistant hypertension. The trial has two arms: the treatment and control (sham group). The treatment group will be submitted to the stimulation procedure (TENS). The sham group will not be submitted to stimulation. The primary outcomes will be a reduction in the peripheral blood pressure and adverse events. The secondary outcomes will be a reduction the central blood pressure. The study will last 30 days. The sample size was calculated assuming an alpha error of 5 % to reject the null hypothesis with a statistical power of 80 %, thereby resulting in 28 participants per group (intervention versus sham).

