### Ambulatory blood pressure monitoring

ABPM will be performed using the Mobil-O-Graph monitoring device (I.E.M. Gmb, Stolberg, Germany) [59]. Monitoring requires patients to maintain their normal daily activities with the BP being measured automatically at 30-minute intervals for an entire 24-h period according to the technical norms of the 5^th^ Guidelines on Ambulatory Blood Pressure Monitoring [60]. The following parameters will be measured and evaluated over 24 h: systolic (SBP) and diastolic BP (DBP), PP, central systolic and diastolic aortic pressure, central PP, AIx, PWV, cardiac output, and peripheral vascular resistance.

The SBP and DBP will be obtained by ABPM with the mean values for the 24-h period, daytime, and nighttime being considered for analysis. RH patients with mean BP values of ≥ 130 × 80 mmHg over 24 h, ≥ 135 × 85 mmHg during wakefulness, and ≥ 120 × 70 mmHg when asleep will be considered. PP will be calculated during the periods (24 h, daytime, and night) using the formula PP = SBP - DBP. The normal nocturnal dip will be defined as a drop >10 % in SBP from wakefulness to the period of sleeping.

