### Assessment of outcomes

Blood pressure (mean of two measurements by an automatic electronic device Omron HEM-711 DLX) and hemodynamic parameters (by Omron HEM 9000 AI device) will be measured in the office at the follow-up visits.

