### Sample size calculation

The site http://www.lee.dante.br/pesquisa/amostragem/amostra.html was used to estimate the sample size. The sample size calculation with a P alpha of 0.05, statistical power of 80 %, standard deviation of 8 mmHg, and maximum acceptable absolute difference of 6 mmHg (diastolic BP), indicated the necessity to study 28 patients per group (intervention versus sham). However, considering a potential 10–15 % dropout or loss to follow-up rate, 32 will be considered for each group. The difference of 5 mmHg (diastolic) has been achieved, on average, in clinical trials that have demonstrated the advantage of a drug over placebo or other nonpharmacological treatment in the prevention of major cardiovascular outcomes.

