### Statistics

All analyses will be performed using SPSS Statistical Software (IBM SPSS Statistics for Windows, Version 21.0. Armonk, NY, USA). Continuous variables will be presented as mean ± SD, and categorical variables, as frequencies. Differences between the groups at baseline will be evaluated by an unpaired *t* test or the Mann–Whitney test for comparison of continuous variables. The Chi-square test or Fisher’s exact test will be employed to compare categorical variables. The change from baseline to 4-week follow-up in the groups will be evaluated using the paired *t* test for continuous variables. Pearson’s correlation will be used to assess the relation between BP reduction and treatment (intervention). For all analyses, a two-sided *P* < 0.05 will be considered statistically significant.

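### The primary outcome, change in peripheral blood pressure, fits four to eight readings that the article collects, and the article does not say which one decides the trial

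*Protocol article*

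**What the plan says.** Five places in the article bear on what the primary variable is.

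- **Primary outcome measure:** "The primary outcome measure will be the change from baseline in the peripheral blood pressure of individuals with resistant hypertension", after stimulation. It does not say systolic or diastolic, office or ambulatory, or over which period.
- **Assessment of outcomes:** "Blood pressure (mean of two measurements by an automatic electronic device Omron HEM-711 DLX") is listed with the haemodynamic parameters, and these "will be measured in the office at the follow-up visits".
- **Ambulatory blood pressure monitoring:** "The SBP and DBP will be obtained by ABPM with the mean values for the 24-h period, daytime, and nighttime being considered for analysis".
- **Sample size calculation:** 28 per group from an SD of 8 mmHg and a "maximum acceptable absolute difference of 6 mmHg (diastolic BP"). It names neither the measurement method nor the source of the SD.
- **Statistics:** for all analyses, a two-sided P below "0.05 will be considered statistically significant". The change is taken from baseline to the 4-week follow-up.

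The abstract's Methods/design paragraph differs from the body on the number of primary outcomes: "The primary outcomes will be a reduction in the peripheral blood pressure and adverse events".

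**The concern.** The outcome section is where a protocol commits itself to one variable. Here its wording fits several variables equally well, and the sections that could narrow it do not agree. An analyst following the article could report office diastolic, 24-h systolic or night-time diastolic BP as the primary result, and a reader could not show that the plan had been departed from.

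Two things are then at stake. The 5% error rate applies to each reading taken alone, and not to the statement that the trial met its primary outcome. The 80% power was worked out for one diastolic comparison, so it says nothing about success on a systolic reading, whose SD and target difference are not given.

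The difference between abstract and body over adverse events is a smaller, separate matter. The two parts of the article do not agree on what is primary.

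**Working it through.** **1. Reproduce the stated sample size.** Inputs from Sample size calculation: difference 6 mmHg, SD 8 mmHg, alpha 0.05, power 80%, two equal groups.

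n per group = 2 × (z₀.₉₇₅ + z₀.₈₀)² × SD² / difference² = 2 × (1.960 + 0.842)² × 64 / 36 = 27.9, so 28.

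This matches the article. A t-based calculation gives 29, and a one-sided test would give 22, so the figure is two-sided. For dropout, 28/0.90 = 31.1 (32) and 28/0.85 = 32.9 (33), so 32 is consistent with the stated 10–15%. The calculation is sound for **one** between-group comparison of **one** diastolic reading.

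**2. Count the readings that fit the definition.**

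| Source | Readings | Count |
|---|---|---|
| ABPM | systolic, diastolic × 24 h, day, night | 6 |
| Office | systolic, diastolic | 2 |
| Total | | 8 |
| If the sample size fixes diastolic BP | office, 24-h, day, night diastolic | 4 |

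**3. Chance of a false primary result if any of k readings may be called primary.** If the readings were independent, the chance of at least one p < 0.05 is 1 − 0.95ᵏ: 33.7% for k = 8 and 18.5% for k = 4. Blood pressure readings from one patient are correlated, so these are upper limits. The article gives no correlations. I therefore assume a common correlation r between the test statistics, each compared between groups at |z| > 1.96:

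| k | r | Any p < 0.05 | In favour of TENS only |
|---|---|---|---|
| 8 | 0.5 | 25% | 12.5% |
| 8 | 0.7 | 19% | 9.5% |
| 8 | 0.8 | 16% | 8% |
| 8 | 0.9 | 12% | 6% |
| 4 | 0.5 | 16% | 8% |
| 4 | 0.7 | 13% | 6.5% |
| 4 | 0.8 | 11% | 6% |
| 4 | 0.9 | 9% | 5% |
| 1 | – | 5% | 2.5% |

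The last column carries the most weight, because the error of concern is a false claim for TENS. Its nominal value is 2.5%.

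**4. What keeping all eight as primary would cost.** With Bonferroni, each test is at 0.05/8 = 0.00625. For the same 6 mmHg and SD 8, the formula in step 1 gives 46 per group before dropout, and 28 per group would have 53% power for each test. Naming one variable restores 5% and leaves 28 per group valid, provided that the variable is a diastolic BP with SD 8.

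**The case against.** The best counter-argument is that the text already narrows the choice. Assessment of outcomes follows directly after the two outcome sections and names one office device and averaging rule, and the sample size uses diastolic BP. Read together, they suggest office diastolic BP. The ambulatory section never calls its means primary. An analysis plan that is not shown may also hold a multiplicity rule, and a 0.05 threshold for all analyses does not declare every reading a primary test.

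Much of this stands. The narrowing to diastolic BP is plausible, which is why the four-reading figures are given beside the eight. If the device were settled but not the component, two readings would remain, and the chance of any p < 0.05 would be 8–9% at r = 0.5 to 0.8. A missing testing order is not itself a fault of the article. But nowhere is diastolic BP or office BP stated to be the primary outcome, and the ambulatory means are expressly up for analysis. Which variable is primary belongs in the outcome definition, and the article has a section for it.

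A reader might go further in three ways that the documents do not support:

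- **Counting more readings.** One could add pulse pressure, the beat-to-beat recording and the HEM 9000 AI values. Nothing labels pulse pressure a primary candidate. The beat-to-beat system is there for sympathetic activity, and the HEM 9000 AI serves arterial stiffness and haemodynamics, where the stiffness parameters are secondary.
- **Treating adverse events as another way to claim efficacy.** No test or success criterion is stated for them, and a safety outcome reported descriptively needs neither a hypothesis nor a power calculation.
- **Concluding that ambulatory BP must be the primary measure.** The article does not settle that, and the section on outcome assessment names office BP.

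**Conclusion.** The point holds. The primary variable is not fixed, and the sections that bear on it do not agree. Up to eight readings fit the wording, four on the more generous reading. The chance of at least one false p < 0.05 is then 16–25% or 11–16%, and of a false claim for TENS 8–12.5% or 6–8% against 2.5%.

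These ranges assume equal correlations of 0.5 to 0.8, no true effect on any reading, and a free choice among the readings. Means of one component over overlapping windows may be more strongly correlated. At 0.9 the figures for eight readings fall to 12% and 6%, still more than twice nominal. The stated power of 80% is correct for a single diastolic comparison and for nothing else. The adverse-event difference is an inconsistency between abstract and body and does not add to these error rates.

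**What to change.** Name one primary variable that matches the sample size: change from baseline to week 4 in diastolic BP, TENS versus sham, two-sided 0.05. State a single method, either the office mean or the 24-h ABPM mean, and choose the one to which the 8 mmHg SD applies. The source of that SD should be given at the same time. Make all other blood pressure readings secondary. Align the abstract with the body by reporting adverse events as a descriptive safety outcome.

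The Trial status section says that randomization has begun, so this should be a dated amendment made before outcome data are examined.

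The cost is small. Office BP is measured at every visit and ABPM is scheduled at weeks 1 and 4 (Table 1), so no new measurement is needed, and 28 per group (32 with dropout) stands. The downside is that the other readings can no longer be claimed as primary results.

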### Secondary outcome measures

The secondary outcome measures from baseline are the arterial stiffness measurement parameters (including central blood pressure) of individuals with resistant hypertension after transcutaneous electrical nervous stimulation.

### Assessment of outcomes

Blood pressure (mean of two measurements by an automatic electronic device Omron HEM-711 DLX) and hemodynamic parameters (by Omron HEM 9000 AI device) will be measured in the office at the follow-up visits.

### Adverse events

The adverse events will be investigated by open questions and by a semistructured questionnaire, which will address general symptoms and the presumed adverse effects of the electrostimulation used in the trial. Laboratory adverse events, such as metabolic changes and inflammatory markers, will be investigated at the final visit of the participants.

### Missing or dropout

Participants will be registered with a phone number and address for further contact in case of missing outlined visits.

### Sample size calculation

The site http://www.lee.dante.br/pesquisa/amostragem/amostra.html was used to estimate the sample size. The sample size calculation with a P alpha of 0.05, statistical power of 80 %, standard deviation of 8 mmHg, and maximum acceptable absolute difference of 6 mmHg (diastolic BP), indicated the necessity to study 28 patients per group (intervention versus sham). However, considering a potential 10–15 % dropout or loss to follow-up rate, 32 will be considered for each group. The difference of 5 mmHg (diastolic) has been achieved, on average, in clinical trials that have demonstrated the advantage of a drug over placebo or other nonpharmacological treatment in the prevention of major cardiovascular outcomes.

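### Minor: 32 per group keeps the required 28 evaluable only up to 12.5% loss, so the upper half of the stated 10–15% range is not covered

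*Protocol article*

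**What the plan says.** The Sample size calculation section of the protocol article gives its inputs as follows: "The sample size calculation with a P alpha of 0.05, statistical power of 80 %, standard deviation of 8 mmHg", and a diastolic difference of 6 mmHg. From these it derives 28 patients per group. The next sentence adds the allowance for attrition: "considering a potential 10–15 % dropout or loss to follow-up rate, 32 will be considered for each group".

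The Statistics section sets the significance rule: "For all analyses, a two-sided *P* < 0.05 will be considered statistically significant".

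The abstract (Methods/design) reports the same calculation in short form, with a "statistical power of 80 %, thereby resulting in 28 participants per group (intervention versus sham"). It mentions neither the attrition allowance nor the 32.

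**The concern.** The figure of 32 is presented as the answer to a stated range of loss. A reader will take it that the trial still has its 28 evaluable patients per group anywhere in that range, and so keeps its 80% power. That can be checked from the article's own numbers, and it fails in the upper half of the range.

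What is at stake is small: whether the stated tolerance for loss is true, and how far power falls if loss reaches the top of the range that the authors themselves foresee.

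**Working it through.** **Inputs, all from the protocol article.** Difference 6 mmHg, SD 8 mmHg, alpha 0.05, power 80%, loss 10–15%, 28 per group before loss and 32 after (Sample size calculation); two-sided testing (Statistics). I assume equal loss in the two groups.

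**Step 1. Reproduce the 28.** For two equal groups under the normal approximation:

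n = 2 × [SD × (z₀.₉₇₅ + z₀.₈₀) / difference]² = 2 × [8 × (1.960 + 0.842) / 6]² = 27.9, rounded up to **28**.

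The article's figure reproduces exactly. The corresponding two-sample t calculation gives 28.9, so 29. The 28 is therefore the normal-approximation result and has almost no slack.

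**Step 2. Number needed to keep 28 after loss d,** n = 28 / (1 − d), and **number left from 32,** 32 × (1 − d):

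| Loss | Needed to keep 28 | Left from 32 |
|---|---|---|
| 10% | 28/0.90 = 31.1 → 32 | 28.8 |
| 12.5% | 28/0.875 = 32.0 → 32 | 28.0 |
| 15% | 28/0.85 = 32.9 → 33 | 27.2 |

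The largest loss that 32 can absorb is (32 − 28)/32 = 4/32 = **12.5%**, the midpoint of the stated range.

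The cruder add-on method, 28 × (1 + d), gives 30.8 (31) at 10% and 32.2 at 15%. The 32.2 becomes 33 if rounded up and 32 if rounded to the nearest whole number.

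**Step 3. Power at the numbers left,** for 6 mmHg, SD 8, two-sided 0.05. Under the normal approximation, power = Φ(6 / (8 × √(2/n)) − 1.960):

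- n = 28: 6 / (8 × √(2/28)) = 2.806, and Φ(0.846) = 80.1%.
- n = 27: 6 / (8 × √(2/27)) = 2.756, and Φ(0.796) = 78.7%.

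| Evaluable per group | Normal approximation | Two-sample t test |
|---|---|---|
| 28 | 80.1% | 78.7% |
| 27.2 (expected at 15% loss) | 79.0% | 77.5% |
| 27 | 78.7% | 77.2% |

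The fall from 28 to 27 is 80.1 − 78.7 = 1.4 points on the first method and 78.7 − 77.2 = 1.5 points on the second.

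**The case against.** The case against making anything of this is strong on size. The article gives a range and a single rounded number, calls the loss potential, and nowhere promises 28 completers at 15%. The 32 is adequate from 10% to 12.5%, and at 15% the expected shortfall is 28 − 27.2 = 0.8 of a patient per arm. Adding 4 to 28 is a 14.3% increase (4/28), which lies inside 10–15% if the allowance is read as a simple add-on; that may be how the 32 arose. A change of about 1.5 points of power is also small beside the uncertainty in an assumed SD of 8 mmHg. The t-test column adds nothing to the charge on its own, because by that method 28 falls short of 80% even with no shortfall.

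Most of this stands, and it fixes the point as minor. It does not make the sentence correct. A dropout rate applies to those enrolled, and 15% of 32 lost leaves fewer than 28 however the 32 was reached. On either method, power at the top of the range is below the stated 80%.

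A reader might also infer something stronger from the abstract: that the article carries two competing trial sizes, 56 in total (2 × 28) and 64 in total (2 × 32), and that power would drop well below 77% if only 28 per group were randomised. The document does not support this. The abstract presents 28 as what the calculation produced, which is the same pre-dropout figure as in the Sample size calculation section; it does not say that 28 will be enrolled or randomised. The body then gives 32 per group as the planned number, so a scenario with 28 randomised is one that the article rules out. Leaving the attrition step out of a condensed abstract is an omission that may mislead someone who reads only the abstract. It is not a contradiction.

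**Conclusion.** Wrong as written, but minor. The 32 per group retains 28 evaluable patients only up to 12.5% loss. At 15% about 27 remain, and power for the planned 6 mmHg difference is about 79% (normal approximation) or about 77% (two-sample t test), not 80%. The deficit is one patient per arm.

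This rests on the article's SD and difference taken as given, equal loss in both groups, and a between-group comparison at two-sided 0.05. The two-sample t test is my assumption for that comparison, since the Statistics section names an unpaired t test only for baseline differences; the normal-approximation figure does not depend on it.

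The abstract is not in error on this point.

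**What to change.** Reword the attrition sentence in the Sample size calculation section along these lines:

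> 32 per group, which retains 28 evaluable with up to 12.5% loss; at 15% loss about 27 remain and power is about 77–79%.

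This costs one sentence and no patients; the stated tolerance for loss becomes slightly less favourable. The alternative, if the sponsor prefers to keep the full 15%, is 33 per group (66 in total instead of 64), one more patient per arm. As the Trial status section says that randomisation has begun, the rewording is the simpler course.

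Optionally, the abstract could add that 32 per group are planned to allow for loss. That is a clarification only.

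### The trial is sized for a 6 mmHg diastolic difference, but the only benchmark cited is 5 mmHg, where power is about 63–65%; the gap is not explained

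*Protocol article*

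**What the plan says.** All the sizing inputs are in the Sample size calculation section of the protocol article. The section opens with "The sample size calculation with a P alpha of 0.05", and goes on to "statistical power of 80" per cent and a "standard deviation of 8 mmHg". The difference and the result come together: "maximum acceptable absolute difference of 6 mmHg (diastolic BP), indicated the necessity to study 28 patients per group". An allowance for 10–15% attrition follows: "dropout or loss to follow-up rate, 32 will be considered for each group".

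The section closes with its one clinical reference point: "The difference of 5 mmHg (diastolic) has been achieved, on average, in clinical trials" that demonstrated an advantage in preventing major cardiovascular outcomes. No sentence links that 5 mmHg to the 6 mmHg used in the calculation.

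The Statistics section sets the significance level: "For all analyses, a two-sided *P* < 0.05 will be considered statistically significant". For change from baseline to 4 weeks it names a paired t test. It names the unpaired t test (or Mann–Whitney) for group differences at baseline, and a Pearson correlation between blood pressure reduction and treatment.

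**The concern.** In a sample size section, a sentence about the difference seen in outcome-changing trials normally supports the target difference. Here it gives a smaller number than the one used. Required sample size varies with the inverse square of the difference, so moving from 6 to 5 mmHg multiplies it by (6/5)² = 1.44. A trial with 80% power at 6 mmHg is clearly weaker at 5 mmHg.

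What is at stake is how a null result is read. The Abstract repeats 28 per group and 80% power without naming any difference. A reader who takes 5 mmHg as the benchmark could assume a 20% risk of missing it, when the risk with 28 per group is about 35–37%.

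**Working it through.** **Inputs.** Two-sided α = 0.05 (Statistics; the sample size section gives 0.05 without sidedness), power 80%, SD 8 mmHg, differences of 6 and 5 mmHg, 28 evaluable and 32 enrolled per group, 10–15% loss (all Sample size calculation).

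**Reproducing the stated figure.** For two means with equal groups, n per group = 2(z₀.₉₇₅ + z₀.₈₀)² × SD² / Δ².

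- Δ = 6: 2 × (1.96 + 0.8416)² × 64 / 36 = 27.9, so 28. This matches the article.
- The one-sided version gives 22, so the calculation was two-sided.
- Power at n = 28, Δ = 6: 80.1% by the normal approximation, 78.7% by the noncentral t.

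**Power at the cited 5 mmHg.** Normal approximation: power = Φ(Δ / (SD × √(2/n)) − 1.96).

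- n = 28: 5 / (8 × √(2/28)) = 2.339; Φ(0.379) = 64.7%. Noncentral t: 63.2%.
- n = 32: 5 / (8 × √(2/32)) = 2.500; Φ(0.540) = 70.5%. Noncentral t: 69.2%.
- n for 80% power: 2 × (1.96 + 0.8416)² × 64 / 25 = 40.2, so 41 (normal), or 42 (t), evaluable per group.

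| Evaluable per group | Power at 6 mmHg (t / normal) | Power at 5 mmHg (t / normal) |
|---|---|---|
| 27 | 77.2% / 78.7% | 61.6% / 63.2% |
| 28 | 78.7% / 80.1% | 63.2% / 64.7% |
| 32 | 84.0% / 85.1% | 69.2% / 70.5% |

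**Attrition allowance.**

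- 28 / 0.90 = 31.1, so 32 covers 10% loss.
- 28 / 0.85 = 32.9, so 15% loss needs 33.
- 32 × 0.85 = 27.2, just under 28.
- The loss that 32 covers is 1 − 28/32 = 12.5%.

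**Baseline-adjusted comparison (ANCOVA), Δ = 5, n = 28, t-based.** Let ρ be the correlation between baseline and follow-up diastolic pressure, with equal variances at both times. The documents do not give ρ; the range 0.3 to 0.8 is an assumption.

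- If 8 is the SD of change, the residual SD is 8 × √((1 + ρ)/2). At ρ = 0.3 this is 6.45 (power 81%); at ρ = 0.8 it is 7.59 (power 68%).
- If 8 is the SD of a single reading, the residual SD is 8 × √(1 − ρ²). At ρ = 0.3 this is 7.63 (power 67%); at ρ = 0.8 it is 4.80 (power 97%).

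**The case against.** The strongest reply is that nothing is miscalculated. The article attaches its 80% to 6 mmHg only, and 28 is right for 6 mmHg. It never calls 5 mmHg its target or the smallest difference worth detecting; it reports 5 mmHg as an average seen elsewhere, which can be read as background. This stands. A reader might infer that the article claims 80% power at 5 mmHg, or that it contains an arithmetic error; the text supports neither. What remains is that the only clinical figure offered differs from the one used, without explanation.

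A second reply is that the power at 5 mmHg is conditional. The article does not say whether 8 mmHg is the SD of change or of a single reading, and the test named for change is a within-group paired t test. Both points are fair. However, the article's own 28 reproduces as a two-group comparison with SD 8, so 63–65% uses the same premise as the stated 80%. The planned Pearson correlation between reduction and treatment would match an unadjusted two-group test of change if treatment is coded by arm, but the article does not say so and it would not adjust for baseline.

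Third, the attrition shortfall is trivial: under one patient per group, about 1.5 points of power at 6 mmHg. It also agrees with simple inflation (28 × 1.15 = 32.2). It merits a corrected sentence and no more.

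Finally, a reader might take "maximum acceptable absolute difference of 6 mmHg (diastolic BP" as a sign of an equivalence design. The Abstract frames the calculation as rejecting a null hypothesis and the number matches a superiority calculation, so this is a matter of wording only.

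**Conclusion.** The point holds as a mismatch between the difference used for sizing (6 mmHg) and the only benchmark cited (5 mmHg). Power is about 79–80% at 6 mmHg with 28 per group. At 5 mmHg it is about 63–65% with 28 and 69–71% with all 32, so even full retention does not close the gap; 80% would need 41–42 evaluable per group. These figures assume a two-sided 0.05 between-group test and that SD 8 applies to the variable compared.

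A reader might also infer that baseline adjustment would restore the power by a known amount. The documents do not support a single figure: over ρ from 0.3 to 0.8, power at 5 mmHg is 68–81% on one reading of the SD and 67–97% on the other. Adjustment is still a better primary analysis than separate within-group tests, which do not compare TENS with sham.

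**What to change.** Keep the enrolment; the Trial status section says randomization has begun. Revise the paragraph as follows:

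1. Either justify 6 mmHg as the difference to be detected, or state power at both differences: about 79–80% at 6 mmHg and 63–65% at 5 mmHg, with 28 per group.
2. Say whether the SD of 8 mmHg is for change or for a single reading.
3. State that 32 per group allows for up to 12.5% loss. At 15% loss about 27 remain, with 77% power (t-based) at 6 mmHg.
4. In Statistics, name a between-group comparison of 4-week diastolic pressure adjusted for baseline (ANCOVA) as the primary test in place of the paired t test, without quoting a power gain unless the correlation and the meaning of the SD are documented.

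The cost is one rewritten paragraph and one changed sentence in Statistics. No more patients or measurements are needed. The price is that the stated power looks less favourable at 5 mmHg.
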